
#### Secondary outcomes

Longitudinal succession in gut microbiota composition, diversity and function during the first 9 months of life by randomisation arm: Longitudinal multi-omic variation will be visualized using PCoA and tSNE plots [54]. Significant cross-sectional differences in multi-omic profiles will be assessed using PERMANOVA. To integrate longitudinal data and control for confounders, we will build MER models that incorporate repeated measures (random effects) and time-invariant covariates (fixed effects).Stool metabolome at 4 weeks of age life by randomisation arm: We will generate semi-targeted stool metabolomics data, which will be used to validate metagenome-constrained community-scale metabolic modelling of the gut microbiota, using the MICOM platform [55], which will be used to estimate metabolomic fluxes for other time points that lack direct metabolomic measurements. For cross-sectional metabolite differential abundance analyses, we will use generalized linear regression (continuous dependent variable) and logistic regression (Boolean dependent variable), with an FDR correction on the *p*-values, adjusting for confounders, like sex, weight, and feeding mode.T cell subsets at baseline, weeks 4 and 36 weeks of life by randomisation arm: We will compare T cell subsets frequencies cross-sectionally between iHEU administering *B. infantis* Rosell®-33 versus placebo using Mann–Whitney U tests, and correlate these data with absolute concentrations of *B. infantis* in the gut microbiota. We will utilize multidimensional scaling of markers expressed on both CD4 + and CD8 + T cells using the metaMDS function and PERMANOVA from the vegan R package [56] to identify multivariate statistical differences in immune markers between treatment groups, using the “adonis” function from the vegan R package [56]. Unsupervised cell population identification will be performed using self-organizing maps and hierarchical clustering as implemented in the FlowSOM and metaclustering R packages [57]. Finally, we will use a MER modeling approach mentioned above to account for repeated measurements and for relevant covariates like feeding status, sex, and gestational age at birth.

#### Exploratory outcomes

Presence of *B. infantis* Rosell®-33 in iHEU stool: We will use Mann–Whitney U tests for analyzing absolute abundances of *B. infantis* Rosell®-33, assessed by qPCR, across treatment groups at each time point, with an FDR correction for multiple comparisons.Infant growth—length for age Z scores (LAZ) at 36 weeks of age: LAZ scores will be generated using Intergrowth-21st software, which adjust for infant gestational age at birth and infant sex [58]. LAZ will be binarized into adequate (LAZ ≥ -1) and inadequate (LAZ < -1) and compared between arms. LAZ as a continuous variable will additionally be used in penalized linear regression models between *B. infantis* abundance will while adjusting for feeding. Finally, we will compare the prevalence of stunting at 36 weeks of age between groups using Chi-squared tests.All-cause infectious morbidity: We will abstract outcome data related to infectious morbidity from participant’s health records throughout the study period and quantify and compare occurrence of infectious morbidity outcomes between randomisation arms. The proportion of infants with at least one all-cause infectious morbidity event will be calculated and compared by randomisation group using a Fisher’s exact test. Univariate logistic regression models will be used to compare risk of infectious morbidity by randomisation group, and multivariate logistic regression models will be used to adjust for confounders including infant birth weight and gestational age at birth.Neurodevelopment: Neurodevelopment will be assessed comprehensively at weeks 24 and 36 of life, e.g. using the Bayley Scales of Infant and Toddler Development, and developmental scores will be compared by randomisation group.

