## Methods and design

### Objectives

The primary objectives of this study are to evaluate the effect of early-life *B. infantis* Rosell®-33 supplementation in iHEU on gut microbiome composition and diversity (objective 1), and markers of intestinal inflammation and microbial translocation (objective 2) at 4 weeks of life, and the effect on Th1 cytokine responses to BCG at 7 weeks of life (objective 3).

The secondary objectives of this study are to evaluate the effect of *B. infantis* Rosell®-33 supplementation on longitudinal succession of the gut microbiota composition, diversity and function, stool metabolome and T cell subset ontogeny during the first 9 months of life.

Exploratory objectives are to evaluate whether *B. infantis* Rosell®-33 supplementation improves infant growth, vaccine responses (including antibody titres) to other early childhood vaccines, all-cause morbidity or neurodevelopment during the first 9 months of life.

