### Outcomes and statistical methods

#### Primary outcomes

Analyses will follow intention-to-treat (ITT) principles comparing the two randomised groups.We will compare Alpha (Shannon) and Beta (Bray Curtis and UniFrac) diversity metrics, calculated from shotgun metagenomic sequencing data for each infant stool sample, between treatment arms at 4 weeks. Cross-sectional abundance differences for taxa and functional genes will be assessed using DeSeq2 (negative-binomial) [50] or Corncob (beta-binomial) [51] regression models, with the Benjamini–Hochberg multiple-test correction on the resulting *p*-values (to control the false-discovery-rate (FDR)) [52]. Regressions will be adjusted for confounders, like sex, weight, and feeding mode.Markers of intestinal inflammation and microbial translocation at baseline, weeks 4, 7 and 36: We will compare markers of intestinal inflammation and microbial translocation (Lipocalin-2 (Lcn-2), soluble CD163 (sCD163), iFABP and lipopolysaccharide binding protein (LBP) measured by ELISA in infant plasma) cross-sectionally at each time point between groups using Mann–Whitney U tests. We will correlate absolute concentrations of *B. infantis* in the fecal microbiome with these markers. We will use a mixed-effects regression (MER) modeling approach to account for repeated measurements and for relevant covariates like feeding status and sex.BCG-specific total net Th1 cytokine producing cells at 7 weeks of life: We will compare frequencies of total net cytokine producing cells in response to stimulation with BCG between arms at weeks 7 using linear regression after adjusting for confounders, like sex, weight, and feeding mode. Additionally, T cell response data will be analyzed by COMPASS [53] to compute a ‘functionality score’ or ‘polyfunctionality score’. This analysis will be a regression model testing the association between functionality or polyfunctionality scores and iHEU (*B. infantis* versus placebo). We will perform two-sided hypothesis testing with alpha = 0.05. If the model shows a significant result (*p* < 0.05), we will perform a series of univariate analyses in which we test for an association between a particular functional profile and arm. Those profiles identified as significantly associated will be incorporated into a multivariate linear regression model, which will include two-way interaction terms. This will allow us to create a model that includes the cytokine-producing profiles that are most associated with the intervention. We will test the classification accuracy of this model using receiver-operative curve (ROC) analysis. In all models, we will include sex, birth weight, and feeding mode as possible confounders.

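### Growth is compared between arms only as yes/no outcomes; no between-arm comparison of continuous week-36 LAZ is specified

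*Protocol article*

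**What the plan says.** The Objectives section of the protocol article sets the question: "Exploratory objectives are to evaluate whether *B. infantis* Rosell®-33 supplementation improves infant growth". That asks about the effect of assignment to supplement or placebo.

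The Exploratory outcomes section names the endpoint, "Infant growth—length for age Z scores (LAZ) at 36 weeks of age", and gives three analyses:

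1. A split at -1: "LAZ will be binarized into adequate (LAZ ≥ -1) and inadequate (LAZ < -1) and compared between arms". No test is named.
2. A model of the continuous score: "LAZ as a continuous variable will additionally be used in penalized linear regression models between *B. infantis* abundance will while adjusting for feeding".
3. Stunting: "we will compare the prevalence of stunting at 36 weeks of age between groups using Chi-squared tests". Stunting is not defined.

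The scores are already standardised for sex and gestational age at birth. Under Primary outcomes the article states its general principle: "Analyses will follow intention-to-treat (ITT) principles comparing the two randomised groups". No other section gives a between-arm analysis of LAZ.

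**The concern.** The two growth analyses that name arm are both binary. The one analysis that keeps LAZ continuous names abundance, not arm, as its exposure. Stool abundance and feeding are both recorded after randomisation, and the Intervention section itself foresees some mothers turning to formula during dosing. An association between abundance and LAZ is therefore observational and does not estimate the effect of assignment.

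Cutting a Z score at -1 ignores how far each infant lies from the cut. If supplementation moves the whole distribution modestly, the specified randomised tests could well miss it, and a null result might be read as no effect on growth. The lengths needed for the fuller comparison are being collected anyway.

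This concerns a stated choice of method. The article gives the cut point, the stunting test, and the exposure and covariate for continuous LAZ.

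**Working it through.** **The plan's own figure.** There is none to reproduce. The Sample size section covers only the three primary objectives and gives no LAZ mean, SD, effect or power.

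**Inputs from the article.** 200 infants randomised 1:1, with 9% lost by week 36: 200 × 0.91 = 182, or 91 per arm. Two-sided alpha of 0.05 is stated for the BCG analysis and assumed here.

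**Assumed inputs.** Normal LAZ, placebo mean 0, -0.5 or -1, SD 1.0 to 1.1, and the same shift of 0.3 or 0.4 SD in every supplemented infant. Stunting is taken as LAZ below -2.

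**Continuous comparison by arm.** Power = Φ(d × √(n/2) − 1.96), with √(91/2) = 6.745.

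- d = 0.3: 2.024 − 1.96 = 0.064, so 52% (0.525 by this formula, 52% by the t test).
- d = 0.4: 2.698 − 1.96 = 0.738, so 77%.

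**Cut at -1 by arm.** With p1 and p2 the proportions below -1, power = Φ((p1 − p2 − 1.96 × se0)/se1). Here se0 uses the pooled proportion and se1 the separate ones. Example with mean -0.5, SD 1, shift 0.4: p1 = 0.309, p2 = 0.184, difference 0.124 before rounding, se0 = 0.0639, se1 = 0.0632. Then (0.124 − 0.125)/0.0632 ≈ −0.01, so about 50%.

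Results with SD 1:

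| Placebo mean LAZ | Placebo share below -1 | Power of cut, 0.3 SD | Power of cut, 0.4 SD |
|---|---|---|---|
| 0 | 16% | 24% | 37% |
| -0.5 | 31% | 32% | 50% |
| -1 | 50% | 36% | 57% |
| Continuous, any mean | – | 52% | 77% |

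SD 1.1 stays within these ranges. Stunting has 9% to 24% power at 0.3 SD and 12% to 37% at 0.4 SD with SD 1.

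**Information kept by the cut.** Relative efficiency is φ(t)²/[p(1 − p)], where t is the standardised cut and p the proportion below it. It is 0.44 at mean 0, 0.58 at -0.5 and 0.64 at -1 (SD 1). The last is the best case, with the cut at the mean, and still loses about 36%.

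**A different effect pattern.** Suppose instead a gain of 0.6 SD only in infants below -1 and none in the rest (simulated, 91 per arm, SD 1). With placebo mean -0.5, power is about 27% for the means and 81% for the cut. With mean -1 it is about 62% and 89%. The ranking reverses.

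**The case against.** Four points on the other side have force.

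*The sentence is corrupted.* A reader might infer that the randomised comparison of continuous LAZ is never made, or that abundance has replaced arm. The text does not support that. The sentence has one term after a word that needs two, and words are plainly missing, so a lost mention of arm cannot be excluded. What can be said is that no such comparison is specified as printed.

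*The abundance model is not offered as the randomised test.* It is introduced as an additional analysis. The article pairs arm comparisons with *B. infantis* correlations elsewhere too, for the inflammation markers and the T cell subsets. This stands: the model is a legitimate look at mechanism and needs only a clear label.

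*The cut may be the better test.* The article calls LAZ below -1 inadequate, and a benefit concentrated in those infants is plausible. The simulation above shows that the cut would then win clearly. So it is too much to call the mean comparison best in general. The cut is also prespecified, so it raises no suspicion of data-driven choice. This argues for reporting both analyses, not for leaving one out.

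*Growth is exploratory, and an article need not list every exploratory model.* This limits the importance. It does not remove the point, because the article lists its growth analyses in some detail. In the same section it compares developmental scores by randomised group with no cut stated.

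**Conclusion.** The concern holds in a limited form. The Exploratory outcomes section specifies between-arm growth comparisons only for LAZ split at -1 and for stunting. Continuous LAZ is tied, in a garbled sentence, to a post-randomisation measure.

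Under a uniform shift of 0.3 to 0.4 SD, the missing comparison would raise power from 24–36% to 52%, or from 37–57% to 77%. These figures rest on an assumed LAZ mean and SD, normality, and above all a uniform shift; the article supplies none of them. Under a normal uniform shift, the direction does not depend on the assumed mean or SD. Under an effect confined to the lower tail it does not hold.

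The binary comparisons are valid randomised comparisons. The importance is minor: no primary conclusion and no sample size figure is touched.

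**What to change.** 1. Repair the continuous-LAZ sentence so that its outcome, exposure and covariates can be read.
2. Add a linear model of continuous week-36 LAZ on randomised arm, reporting the mean difference with 95% CI as the main growth estimate.
3. Adjust that model for a size measure that clearly precedes treatment. Birth weight qualifies. Length qualifies only if taken before the first dose: the Participant timeline section lists the enrolment examination without length and places length measurement thereafter, while product starts on day 1–3. The schedule table is not shown, so this needs checking. Sex need not be added for standardisation, since LAZ already accounts for it.
4. Keep the -1 split and stunting as prespecified supportive comparisons.
5. Label the abundance regression a non-randomised association.

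The cost is a few lines of wording, best settled before unblinding, and one more exploratory analysis to report. Length is already scheduled at the follow-up visits, so no new data are needed.

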**Methods:**

This is a parallel, randomised, controlled trial. Two-hundred breastfed iHEU will be enrolled from the Khayelitsha Site B Midwife Obstetric Unit in Cape Town, South Africa and 1:1 randomised to receive 8 × 10^9^ CFU *B. infantis* Rosell®-33 daily or placebo for the first 4 weeks of life, starting on day 1–3 of life. Infants will be followed over 36 weeks with extensive collection of meta-data and samples. Primary outcomes include gut microbiome composition and diversity, intestinal inflammation and microbial translocation and cellular vaccine responses. Additional outcomes include biological (e.g. gut metabolome and T cell phenotypes) and clinical (e.g. growth and morbidity) outcome measures.

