### Sample size

We propose to enrol 200 iHEU based on sample size calculation conducted for each of the three primary objectives.Objective 1: Sample size calculations were based on metagenomic data from D’Souza et al. (2020) [44], and on *B. infantis* copies in the stool collected at day 4–7 of life from infants in our current observational cohort from the same clinical site, where the mean *B. infantis* copy number was 3000 per 2.5 ng gDNA. The power analysis was based on a generalized linear regression approach, with a betabinomial error model for the dependent variable where varying effect sizes were injected to calculate effective power. The sample size of 100 iHEU per group is adequately powered to detect a difference of at least twofold for differential abundance testing and R^2^ values of 0.01 or higher in PERMANOVA analyses between iHEU administering *B. infanti*s Rosell®-33 versus those administering placebo, even after accounting for a lost-to-follow-up rate of 9% at week 36 (based on our observational cohort).Objective 2: Based on data from our observational cohort where the mean log intestinal fatty-acid binding protein (iFABP) plasma concentration in iHEU at day 4–7 was 0.454 ng/ml with a standard deviation of 0.164, we will have 80% power to detect a 20% difference in iFABP with *n* = 51 per group. Therefore, our proposed sample size of *n* = 100 per group will be ample to detect what we think is a meaningful difference.Objective 3: A sample size of 78 per group (total *n* = 156) will provide 80% power to detect a 45% increase in total net Th1 cytokine responses to BCG based on preliminary data in iHEU where the mean response was 0.78 and standard deviation 0.8, and the proposed sample size of 100 iHEU per arm accounts for a predicted loss-to-follow-up rate of 2.5% to 7 weeks, resulting in an expected sample size of *n* = 195 at week 7.

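### Infectious morbidity is analysed only as any event versus none, so repeat infections and unequal follow-up go unused; a prespecified event-rate comparison would be a cheap improvement

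*Protocol article*

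**What the plan says.** The Exploratory outcomes section of the protocol article takes infectious morbidity from participants' health records throughout the study and says the trial will "quantify and compare occurrence of infectious morbidity outcomes between randomisation arms". It then names the methods:

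- Fisher's exact test, applied to the any-event indicator: "The proportion of infants with at least one all-cause infectious morbidity event will be calculated and compared by randomisation group".
- Logistic regression, first unadjusted: "Univariate logistic regression models will be used to compare risk of infectious morbidity by randomisation group". A multivariable version follows, with birth weight and gestational age among its covariates.

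No count, rate, time-to-event or recurrent-event analysis is named for this outcome, and no person-time offset.

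Three other places bear on the point. The Abstract says "Infants will be followed over 36 weeks with extensive collection of meta-data and samples". The Sample size section expects a "lost-to-follow-up rate of 9% at week 36". The same section also says "We propose to enrol 200 iHEU based on sample size calculation conducted for each of the three primary objectives", so morbidity, listed under the exploratory objectives, had no part in setting the sample size.

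**The concern.** The data collected are richer than the analysis named for them. Events are abstracted over up to 36 weeks, and under Participant timeline infant health is reviewed at each visit by interview and folder review. Reducing this to one indicator per infant has two consequences.

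- **Repeat infections are ignored.** If most infants have at least one recorded infection, both proportions move towards 100% and the contrast between arms shrinks, even when the number of infections differs clearly.
- **Follow-up time is ignored.** An infant lost early with no event is treated like one observed event-free to week 36.

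The article handles another exploratory outcome differently: length-for-age is dichotomised but also analysed as a continuous variable. Morbidity has no such companion analysis, although the Background rests on excess infectious morbidity in these infants. What is at stake is the chance of seeing an effect on infection burden in data the trial will already hold.

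A smaller point is that logistic regression, described as comparing risk, produces odds ratios. These lie further from 1 than risk ratios when the outcome is common.

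**Working it through.** The article states no event rate, effect or power for this outcome, so there is no figure of its own to reproduce. The check compares the named tests with a rate analysis under stated assumptions.

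**Inputs from the article:** 100 infants per arm and 9% lost by week 36, so 100 × 0.91 = 91 per arm. Two-sided alpha of 0.05 is stated for the T cell analysis and assumed here.

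**Assumptions (not in the article):** control mean μ0 of 0.2 to 3 recorded events per infant; negative-binomial dispersion k of 0 to 2; a constant rate ratio, 0.7 in the main runs, so μ1 = 0.7 × μ0.

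**Formulas**

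- Probability of at least one event: 1 − (1 + kμ)^(−1/k), or 1 − e^(−μ) when k = 0.
- Any-event analysis: exact power of Fisher's test, and the large-sample two-proportion test as a stand-in for unadjusted logistic regression.
- Rate analysis: Wald test of the log rate ratio, with variance (1/μ0 + 1/μ1 + 2k)/n.
- Relative loss: 1 − (any-event power)/(rate power).

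**One case in full (μ0 = 1, μ1 = 0.7, k = 0.5)**

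- Any-event proportions: 1 − 1.5^(−2) = 0.556 and 1 − 1.35^(−2) = 0.451. Fisher power is 23%; two-proportion power is 29%.
- Rate test: SE = √((1 + 1.429 + 1)/91) = 0.194 and |ln 0.7| = 0.357, so z = 0.357/0.194 − 1.96 = −0.12 and power is 45%.
- Loss: 49% with Fisher, 36% with the two-proportion test. The gap between the two losses comes from Fisher's conservatism, not from dichotomising.

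**Across infection rates (rate ratio 0.7, k = 0.5, 91 per arm)**

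| Control mean events | Rate | Fisher | Two-proportion | Loss, Fisher | Loss, two-proportion |
|---|---|---|---|---|---|
| 0.2 | 15% | 10% | 14% | 33% | 8% |
| 0.5 | 29% | 19% | 23% | 35% | 21% |
| 1 | 45% | 23% | 29% | 49% | 36% |
| 2 | 63% | 24% | 29% | 61% | 54% |
| 3 | 72% | 21% | 26% | 71% | 64% |

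Rate power rises with the number of events; any-event power levels off and then falls.

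**Sensitivity to dispersion and effect**

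- Rate ratio 0.7, k from 0 to 2: the Fisher loss is 29–44% at 0.2 to 0.5 events, 40–53% at 1, 53–67% at 2 and 67–71% at 3.
- Rate ratio 0.65, same formulas: 26–53% at 1 or fewer events, 40–67% at 2 and 52–71% at 3. The 40% is the case without overdispersion: proportions 1 − e^(−2) = 0.865 and 1 − e^(−1.3) = 0.727, Fisher 57% against rate 95%.
- Rate ratio 0.6, k = 0, 2 events: the loss is only 26%, because the rate test is already near its ceiling (73% against 99%).

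**Simulation with unequal follow-up** (100 per arm, 9% lost at uniform times, robust variance, rate ratio 0.7): Fisher losses were 29–47% at 0.2 to 0.5 events, 37–57% at 1, 56–63% at 2 and 66–73% at 3. With no effect, the rate test rejected in about 4% to 6.5% of runs and Fisher's test in 2.5% to 4.5%.

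**Effect limited to the first third of follow-up** (rate ratio 0.65, then 1): power was about 16% or less for every test. The rate analysis was still no worse than the others.

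**Odds ratio illustration** (assumed proportions 73% and 61%): risk ratio 0.61/0.73 = 0.84; odds ratio (0.61/0.39)/(0.73/0.27) = 0.58.

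**The case against.** The strongest reply is that this is a valid, if less efficient, analysis of an exploratory outcome for which the article claims no power. Having at least one infection is a meaningful quantity, and it needs no rule for separating a new episode from a repeat visit. The general promise to compare occurrence leaves room for a count analysis in a full protocol or statistical analysis plan that is not shown. This limits how serious the point is, but does not remove it. The article does not stay silent on method: it names the tests, all of them binary, and attaches nothing else to that promise.

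A reader might infer that the choice costs half or more of the power. The article does not support that as a fact, since it gives no infection rate, dispersion or effect. Nor does it show that most infants will have a recorded infection. The Background's statement that infections are more common than in unexposed infants is relative, and eligibility is restricted to term infants without complications whose mothers plan to breastfeed exclusively. A low recorded rate fits the text as well as a high one, and the loss is then smaller.

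Two further criticisms of the power comparison stand. The tests were not matched on actual type I error, which favours the rate test somewhat. The main runs also assume the same effect throughout follow-up, although the product is given only for about the first four weeks.

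On odds ratios, the article never says one will be presented as a risk ratio, and the proportions will be shown. That part is minor.

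**Conclusion.** The point holds in a limited form. Every method named for infectious morbidity uses a yes/no outcome without person-time, and in the scenarios computed a rate analysis did at least as well, usually clearly better.

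The size depends on assumptions the article cannot settle. With a constant rate ratio of about 0.65 to 0.7, Fisher's test loses roughly a quarter to a half of the power at one or fewer recorded events per infant, and about half to two thirds or more at two to three events (40% at two events in the most favourable case, without overdispersion). For logistic-type testing at a rate ratio of 0.7, the loss is under about 30% at 0.5 or fewer events and reaches half only near two or more. With an early, fading effect neither approach has useful power.

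The outcome is exploratory and no stated power is wrong, so this is a cheap improvement rather than an error that threatens the trial's conclusions.

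**What to change.** Add a prespecified comparison of infectious event rates by arm: negative binomial regression, or Poisson with robust standard errors, of the event count on arm with log follow-up time as offset. Birth weight and gestational age can carry over as covariates in the adjusted model. Write a rule for when a record counts as a new episode, and have it set and applied by staff blinded to arm.

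Keep the any-event proportion alongside the rate, reported as a risk difference or risk ratio (for example, standardised from the logistic model).

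The cost is the episode rule and slightly more analysis work. No new data should be needed if event dates are abstracted with the events, which the team should confirm. Both additions should be fixed before unblinding.
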